## Abstract

**Abstract:**

**Introduction:**

Pharmacogenomic testing could potentially reduce the number of adverse drug reactions and improve treatment outcomes through tailoring treatment to an individual’s genetic makeup. Despite its benefits and the ambitions to integrate into routine care, the implementation of pharmacogenomic testing in primary care settings remains limited. This study aims to qualitatively explore the views of healthcare professionals (HCPs) and patients on implementing pharmacogenomic testing in the UK National Health Service (NHS) primary care setting and to estimate the cost-effectiveness of service-delivery implementation by comparing different HCPs’ models of care.

**Method:**

This study consists of three workstreams (WS). WS1 is semi-structured interviews with General Practitioners, pharmacists, nurses and patients (24 participants) to explore implementation issues, including the perceived barriers and facilitators to delivering a pharmacogenomic service. WS2 consists of focus groups (between 24–36 participants) with genomic experts to develop practical pharmacogenomic-guided clinical pathways for primary care. WS3 will estimate the cost-effectiveness of implementing pharmacogenomic testing when led by different HCPs incorporating parameters from the literature, expert opinions, as well as data from WS1 and WS2.

**Analysis:**

Thematic analysis will be used to analyse the qualitative data from WS1 and WS2, mapping findings onto the Consolidated Framework for Implementation Research domains, which will also be used as the theoretical framework. WS3 will be a decision-analytic model developed in Microsoft Excel to compare the cost-effectiveness of pharmacist-led, GP-led, nurse-led or multidisciplinary pathways.

**Ethics and dissemination:**

This study has been approved by the NHS Health Research Authority and Health and Care Research Wales (24/PR/1088). Findings will be disseminated through peer-reviewed publications, conference presentations and engagement with NHS policymakers and Genomics England.

STRENGTHS AND LIMITATIONS OF THIS STUDYThis is a mixed-methods study triangulating qualitative findings with the literature to inform an economic model.This study is ‘theory-driven’, informed using a theoretical framework (Consolidated Framework for Implementation Research).The data collected and the resulting economic model may only be applicable to the UK National Health Service primary care setting.Participation in the qualitative work (interviews and focus groups) was limited to self-selected individuals and those who spoke English.The data captured and the model are cross-sectional, and there is no objective assessment of their applicability or evaluation in the long term.

## Introduction

 Pharmacogenomic (or pharmacogenetic) testing aims to optimise prescribing to improve treatment outcomes by maximising the benefit of treatment and/or minimising the risk of harm based on genomic information.^1^ The National Health Service (NHS) in the UK has the ambition to be the first healthcare system to mainstream the use of pharmacogenomics, including in the primary care setting.^2^

Pharmacogenomic testing has the potential to identify individuals with a genetic predisposition to adverse drug reactions (ADRs) or non-response and hence facilitate safer and more effective prescribing. Pharmacogenomic testing will be particularly important for primary care, as 90% of healthcare is delivered through this setting.^3^ A systematic review^4^ in 2021 estimated the incidence of ADRs in primary care at approximately 8% with higher rates seen in very young children, older adults and females. The estimated cost to the NHS for these ADRs is approximately £2 billion per year.^5^ Pharmacogenomic testing offers the potential to mitigate the occurrence of ADRs by predicting an individual’s response to a specific medicine.^6^ This enables the clinician to alter the drug dosage or substitute with a complementary medicine, thereby reducing the incidence of ADRs,^6^ improving efficacy, minimising clinic visits and improving adherence.^7 8^ The focus of most current pharmacogenomic tests has been in the context of reducing the likelihood of ADRs.^9^ However, pharmacogenomic information can also help improve drug effectiveness. For example, some drugs need to be activated by enzymes in the body, and genetic differences can affect how well this happens, such as CYP2D6 with codeine or CYP2C19 with clopidogrel; or genetic changes in drug targets can influence how well a drug works, such as VKORC1 (vitamin K epoxide reductase complex subunit 1) with warfarin or CFTR (Cystic Fibrosis Transmembrane Conductance Regulator) with ivacaftor. Collectively, these factors highlight the growing relevance of pharmacogenomic testing in primary care.

The clinical utility of certain single drug-gene pharmacogenomic tests relevant for primary care has been demonstrated in clinical trials, for example, warfarin for atrial fibrillation^10^ and pharmacogenomic testing in mental health disorders.^11^ Furthermore, the clinical utility of a multigene pharmacogenomic panel was established by the PREPARE study,^6^ which demonstrated that pharmacogenomic testing can reduce ADRs by 30% for patients prescribed certain medicines. This reduction could potentially lead to fewer repeat visits to primary care and thereby ease pressures on general practice by freeing up time and resources. Such benefits are particularly relevant given the current strain on general practitioner (GP) appointments in primary care, the ageing population and the increasing prevalence of patients with multiple long-term conditions.^12^ These demographic and clinical trends often result in polypharmacy and consequently increased risk of ADRs.^13^ Economic evidence is similarly encouraging; a recent systematic review^14^ reported that 71% of 108 studies found pharmacogenomic testing for drugs with existing guidelines to be either cost-effective or cost-saving.

For the purpose of this study, primary care in the UK consists of general practices and community pharmacies. Traditionally, the general practice model included GPs and nurses. However, over the past decade, general practice has seen an expansion of different healthcare professionals (HCPs) working collaboratively. These HCPs include pharmacists, pharmacy technicians, healthcare assistants, physician assistants, physiotherapists and paramedics, with many of these HCPs having prescribing rights. Therefore, understanding the roles of these diverse HCPs in primary care is crucial for the successful implementation of pharmacogenomic testing, as their involvement in patient care and prescribing decisions will shape how pharmacogenomic information is integrated into routine practice.

Although the clinical and cost-effectiveness of a number of pharmacogenomic tests has been demonstrated through various systematic reviews,^15 16^ implementation issues remain. To ensure an efficient and uniform uptake of pharmacogenomic testing across primary care, it is essential to identify the barriers and facilitators to implementation and determine which HCPs should coordinate its delivery. Several international studies have identified these barriers and facilitators;^17^ however, a UK NHS study involving the range of primary care HCPs and patients about these barriers and facilitators is lacking.^18^ Moreover, given the current financial constraints facing the NHS, it is important to understand the costs and value of implementing pharmacogenomic testing in primary care.

### Aims and objectives

This study aims to investigate the perceived barriers and facilitators to the implementation of pharmacogenomic testing in the UK primary care setting. Furthermore, it seeks to assess the value of implementing such testing when led by GPs, pharmacists or nurses.

This study is divided into three workstreams (WS) with the following objectives:

**WS1**—To explore the views of UK patients and HCPs, which includes GPs, practice pharmacists, community pharmacists and practice nurses, regarding the perceived barriers and facilitators for the implementation of pharmacogenomics into routine primary care practice, using the Consolidated Framework for Implementation Research (CFIR).**WS2**—To build on the findings of WS1 to develop pharmacogenomic-guided clinical pathway(s)/workflow(s). HCPs with expertise in genomics and patients will consider the operational changes for implementation, as well as the division of roles and responsibilities through relevant stakeholder engagement.**WS3**—To estimate the cost-effectiveness of implementing pharmacogenomic testing in primary care led by GPs, pharmacists or nurses.

## Methods and analysis

This study began in September 2024 and is due to continue until September 2026. The study will employ a mixed methods approach involving three WS. These are outlined below and then described in more detail.

**WS1** will involve semi-structured interviews with HCPs, including GPs, pharmacists, nurses and patients.**WS2** will involve focus groups, both conducted with HCPs and patients. In conjunction with WS2.**WS3** will develop several models of pharmacogenomic-guided clinical pathways to estimate the cost-effectiveness of implementation by different HCPs. These model pathways will be presented to participants in the focus groups of WS2.

### Qualitative methods

#### WS1: semi-structured interviews with HCPs and patients

##### Recruitment

This WS will focus on the views of GPs, pharmacists, practice nurses and patients. Participants will be recruited using a purposive sampling method, which is a non-probability approach, to ensure a diverse representation across various demographics. Recruitment for the study will include contact and promotion through the main researchers’ professional networks in primary care (including contacts through previous employment and membership of genomics networks), supervisor contacts, circulation of study flyers via high street pharmacies, GP surgeries, social media, through regional Research Design Networks and snowball sampling.

Eligibility criteria include those HCPs currently working in primary care and patients >18 years of age and receiving medicines from their GP. WS1 will recruit twenty-four participants, including six GPs, three practice-based pharmacists, three community pharmacists, six nurse prescribers and six patients. The study aims to include participants from a wide range of demographics, including age, years since qualifying, gender and ethnicity, to ensure a wide range of opinions are included. Twenty-four participants were considered a sufficient sample size due to the specific aims of the study,^19^ other qualitative studies have used a similar sample size,^17^ and this participant size is considered sufficient to reach data saturation.^20 21^ A systematic review by Hennink and Kaiser^22^ suggests that most qualitative studies can reach saturation at relatively small sample sizes. Furthermore, this sample size was chosen based on the pragmatic decision of available resources and timelines.

##### Data collection

Qualitative data will be collected through semi-structured interviews, expected to last between 45–60 mins. Interviews will be offered either online via MS Teams or face-to-face, depending on the participants’ preference. Interviews will be recorded on an encrypted audio device. Written consent to participate will be obtained prior to the interview. Recordings will be stored on a secure server. Interview scripts will be transcribed, anonymised and coded. Interview guides for patients and HCPs will be developed separately and reviewed by the supervisory team (see onlinesupplemental files 1  2). Questions will explore the perceived barriers and facilitators for implementing pharmacogenomic testing in primary care, focusing on the unique challenges of how different HCPs could integrate pharmacogenomics into their roles and responsibilities to optimise patient care. Demographic information, including age, sex, ethnicity and education level, will be collected from each participant before the interview.

### WS2: focus groups with genomic experts, stakeholders and patients

The focus of WS2 is to present a series of plausible HCP-led pharmacogenomic-guided clinical pathways to a panel of experts and patients to evaluate their practicality, feasibility and cost for use in primary care.

#### Recruitment

Four focus groups will be set up, each with 6-9 participants. These participants will include GPs, pharmacists and nurses with some expertise in genomics, commissioners, medical directors, chief pharmacists, laboratory scientists, specialists from secondary care and patients. Each focus group will be heterogeneous with diverse participants, to ensure different opinions are explored. A similar recruitment strategy to WS1 will be employed for WS2, but with an emphasis on recruiting HCPs with some genomics expertise. The sample size of the focus groups is considered sufficient to generate sufficient data to meet the aim of this WS. Guest *et al*^23^ have suggested that 80% of all themes are discovered within 2–3 focus groups.

#### Data collection

Each focus group will last a minimum of 90 mins and up to a maximum of 120 mins. The focus groups will be offered either online via MS Teams or face-to-face, depending on the participants’ preference and convenience. Interviews will be recorded on an encrypted audio device and supplemented with handwritten notes. Participants will be given an identifying code to enable anonymisation (eg, GP1, P1, N1, etc). The main barriers and facilitators defined in WS1 will be ordered into emerging themes and used to further define the needed actions, roles and responsibilities of the primary care team. A script including an introduction to pharmacogenomics, case scenarios and presentation of a model (see onlinesupplemental files 3  4) will be developed and participants will be asked to discuss the themes in the focus group. All data will be anonymised. Results from the focus group and semi-structured interviews will be used to develop proposed pharmacogenomic-guided clinical pathways for use in primary care.

### Qualitative data analysis for WS1 and WS2

Data obtained from the semi-structured interviews and focus groups will be transcribed verbatim and checked by the main researcher. NVivo 15 will be used to organise the data, facilitate coding and help with the analytical process. Data analysis will start during the early stages of data collection and proceed iteratively so that emergent findings are incorporated into subsequent data collection.

All transcripts will involve initial coding through an inductive approach. This will include initial reading and re-reading of the anonymised transcribed data by the main researcher to identify common codes and categories and to develop a coding frame. Codes will then be grouped into emerging themes using Braun and Clarke^20^ and King *et al*^21^ guidance on conducting thematic analysis. These codes and themes will be reviewed by the supervisory team through regular monthly meetings.

The themes will then be mapped to the CFIR to assess the emerging barriers and facilitators of implementation. The CFIR is a conceptual framework that was developed to integrate various implementation science theories into a single, comprehensive model. The CFIR is composed of five domains, including:

Intervention characteristics—features of pharmacogenomic testing.Inner setting—features of primary care/general practice in the UK.Outer setting—NHS.The individuals—GPs, pharmacists, nurses and patients.The process—strategies to influence the implementation of pharmacogenomics.

There are multiple constructs under each domain providing a systematic approach to identifying factors that influence the implementation of an intervention. The framework is an ideal tool to study a complex intervention such as pharmacogenomic testing, which will involve multiple stakeholders, workflows and systems. Compared with other theoretical frameworks, it is well suited for exploring roles, responsibilities and organisational changes.^24^

#### WS3: Decision-analytical modelling

The objective of WS3 is to estimate the cost-effectiveness of potential pharmacogenomic pathways in primary care. With the recent expansion of the primary care team, an increasing proportion of prescribing is undertaken by non-medical prescribers. However, there is uncertainty regarding the cost-effectiveness of different models of care for delivering pharmacogenomics in primary care.

Background work for WS3 will commence prior to WS2, with the purpose of presenting a model to the focus group for discussion. Data generated from WS1 will be used to populate the model. For the focus groups in WS2, this initial model will be presented for discussion and then amended as suggested by the focus groups. The initial phase will involve systematically mapping the steps to incorporate pharmacogenomic testing into the primary care workflow. Figure 1 displays some exemplar pharmacogenomic-guided clinical pathways. These pathways are by no means exhaustive, and the focus groups will be encouraged to amend, adapt or propose new pathways. A consensus on practical pathways will be sought through engagement and agreement with the focus group participants.

**Figure 1 F1:**
[figure not shown]
Displays some exemplar pharmacogenomic-guided clinical pathways. GP, general practitioner.

A review of the literature will be conducted to identify the proposed process steps, such as pretest counselling, ordering the pharmacogenomic test and actions based on the test results. Once the process steps are mapped out, a matrix will be developed to categorise various pharmacogenomic testing models based on the HCP leading the process (eg, GP-led, pharmacist-led, nurse-led).

A decision-analytic model will be developed in Microsoft Excel to compare the cost-effectiveness of the pharmacist-led, GP-led, nurse-led or multidisciplinary approaches. This model will align with the National Institute for Health and Care Excellence (NICE) technology evaluation methods.^25^

##### Population of interest

HCPs including GPs, practice pharmacists, community pharmacists and nurses who can conduct and interpret pharmacogenomic testing in the UK primary care setting (general practice and community pharmacies).

##### Intervention

Pharmacogenomic test-guided prescribing conducted and interpreted by a GP, pharmacist, nurse or a combination of primary care professionals.

##### Comparator

Standard prescribing practices in primary care, where prescribing is undertaken by a GP without pharmacogenomic guidance.

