### Analytical strategy

A decision analytic model will be constructed for a cohort of typical general practice hosting GPs and non-medical prescribers. The cohort will be modelled over a lifetime. The model will have a structure which reflects a typical patient journey through a GP practice. The model seeks to address the issue of technical efficiency—what is the most efficient model of service delivery, as opposed to allocative efficiency (whether testing is undertaken) and as such, the comparators will be alternative HCPs delivering the service. The intervention will be the use of a pharmacogenomic test to guide prescribing by a prescriber (GP or non-medical). A systematic literature review including existing economic evaluations, randomised controlled trials, observational studies and meta-analyses will be undertaken to inform the inputs of the model. Where there is a gap in the literature, the expert focus group in WS2 will be engaged to inform the inputs in the model. All costs and outcomes will be discounted at 3.5% per annum (as recommended by NICE).

The cost-effectiveness of the new way of working will be calculated using the incremental cost-effectiveness ratio, which is the difference in costs between the intervention and standard care divided by the difference in effect between the intervention and standard care. This will be compared with NICE thresholds for cost-effectiveness.

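### With GP-only prescribing as standard care, the ICERs of non-GP-led pathways combine the effect of the test with the effect of changing the prescriber, and the plan names two different comparators

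*Protocol article*

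**What the plan says.** All places are in the protocol article, in the WS3 part of the methods.

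- **Comparator:** standard primary care prescribing, "where prescribing is undertaken by a GP without pharmacogenomic guidance".
- **Intervention:** "Pharmacogenomic test-guided prescribing conducted and interpreted by a GP, pharmacist, nurse or a combination of primary care professionals". The WS3 text after Figure 1 says that the model will "compare the cost-effectiveness of the pharmacist-led, GP-led, nurse-led or multidisciplinary approaches".
- **Analytical strategy, first paragraph:** the question is technical efficiency, that is, which delivery model is most efficient and not whether to test, and so "the comparators will be alternative HCPs delivering the service".
- **Analytical strategy, second paragraph:** the ICER is "the difference in costs between the intervention and standard care divided by the difference in effect between the intervention and standard care", and it is set against NICE thresholds.
- **Current practice:** the opening of WS3 says that "an increasing proportion of prescribing is undertaken by non-medical prescribers", and the Analytical strategy models a practice containing both GPs and non-medical prescribers.
- **Costs:** clinicians' consultation time is included. No unit costs, consultation lengths or test cost are given.

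**The concern.** A pharmacist- or nurse-led tested pathway set against GP prescribing without the test changes two things at once: whether the test is used and who prescribes. Because clinician time is costed, a change of prescriber enters the ICER numerator, although it could be made without any test. The article describes no arm in which a non-GP professional prescribes untested.

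GP-only prescribing also does not match the plan's own account of the modelled setting, where non-medical prescribers are already at work. Part of the skill-mix change would be counted as new when it has already happened.

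At stake is the threshold conclusion for non-GP-led pathways. A reader told that nurse-led testing falls below a threshold could not tell how much of that result is due to the test.

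**Working it through.** The plan states no figure on this point, so there is nothing to reproduce. The check is a decomposition followed by two illustrations with assumed inputs.

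**1. Decomposition.** Write C(p, t) for the cost with prescriber p and test status t (1 = tested, 0 = untested). For a pathway led by a non-GP professional X:

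C(X,1) − C(GP,0) = [C(X,1) − C(X,0)] + [C(X,0) − C(GP,0)]

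The first bracket is the effect of the test. The second is the effect of the prescriber, and it vanishes only if X and the GP cost the same. QALYs split in the same way. For the GP-led pathway the contrast is C(GP,1) − C(GP,0), which contains the test alone.

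**2. Differences between pathways.** With any common baseline S:

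(C(X,1) − S) − (C(GP,1) − S) = C(X,1) − C(GP,1)

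S cancels, for QALYs as well. The choice of baseline does not alter cost or QALY differences between tested pathways.

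**3. Size per episode (assumed inputs).** Take a staff-cost gap of £40-£120 per hour and 10-30 minutes of prescriber time.

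- Low: £40 × 10/60 = £6.67
- High: £120 × 30/60 = £60

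**4. Effect on an ICER (all inputs assumed).** GP prescribing costs £50, the test £100, downstream savings are £40 and the QALY gain is 0.003. The prescriber has no effect on QALYs, and X costs s less than the GP. Like for like, the ICER is (100 − 40)/0.003 = £20,000 per QALY. Against GP-only care, the X-led ICER is (60 − s)/0.003:

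| s (saving with X) | X-led ICER vs GP-only care | GP-led ICER |
|---|---|---|
| −£10 (X dearer) | £23,333 | £20,000 |
| £0 | £20,000 | £20,000 |
| £10 | £16,667 | £20,000 |
| £20 | £13,333 | £20,000 |
| £40 | £6,667 | £20,000 |

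What the test does is identical in every row.

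**5. Effect of a mixed baseline.** If a share m of untested prescribing is already done by X, the baseline cost is C(GP,0) − m·s. The prescriber term in the X-led cost difference becomes −(1 − m)s instead of −s, and the GP-led difference acquires a term +m·s. The gap between them remains s. A mixed baseline therefore describes current practice correctly but does not by itself isolate the test, so a separate same-prescriber scenario is also needed.

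**The case against.** The strongest reply is that the Analytical strategy sets aside whether to test and asks which professional should deliver the service. On that question testing is constant, the baseline cancels (step 2) and nothing is confounded. The ICER might also be read as that of a whole new service, with a cheaper prescriber as part of the package. Further, the GP-led pathway already isolates the test, and X-led minus GP-led testing gives the prescriber effect if test and prescriber do not interact. Finally, the model is provisional: focus groups may amend it, and sensitivity analyses are planned.

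Much of this stands. Comparisons between pathways are sound, and the planned arms permit a separation, though the article does not say that it will be reported. The reply does not remove the point, because the same section goes on to calculate the ICER against standard care and take it to NICE thresholds, while the Time horizon section frames the contrast as guided versus standard prescribing. Even under the package reading, GP-only care is a poor baseline where non-medical prescribing already occurs.

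Three stronger readings are tempting but unsupported:

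- **That the design favours non-GP-led testing.** This needs non-GP care to cost less overall. Longer consultations or referral back to the GP could reverse the sign.
- **That the pathways cannot be compared with one another.** They share a baseline, so their cost and QALY differences are intact. Only the content of each ICER against standard care differs.
- **That the distortion is large over a lifetime.** One affected episode a year for 20 to 40 years, discounted at 3.5% with the first undiscounted, gives multipliers of 14.71 and 22.10, hence £6.67 × 14.71 = £98 to £60 × 22.10 = £1,326. But WS3 describes a professional leading steps such as counselling, ordering the test and acting on results. It does not say that this person takes over later prescribing. Nor can any such total be set against a test cost, since none is given.

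**Conclusion.** The point holds for pharmacist-, nurse- and mixed-led pathways: their ICERs against standard care, which are the ones taken to NICE thresholds, combine a test effect and a prescriber effect. The GP-led ICER against GP-only care and the differences between tested pathways are unaffected. Two inconsistencies in the text are certain and need no assumption: the comparator is stated as GP-only standard care in one place and alternative professionals in another, and GP-only prescribing does not fit the plan's own description of current practice.

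Direction and size are not known from the document. Under the assumed hourly gaps and minutes, the prescriber component is about £7-£60 per affected episode. Any lifetime total depends on an assumed number of episodes. In the assumed example, £10 of prescriber cost moves the ICER by £3,333 per QALY (10/0.003), which could change a threshold conclusion when the QALY gain is small.

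**What to change.** Reconcile the Comparator section with the Analytical strategy. Make the primary analysis a full incremental comparison of all pathways against one common baseline: prescribing without pharmacogenomic guidance by the current mix of GP and non-medical prescribers. The document gives no figure for that mix, so source it and vary it in the deterministic and probabilistic sensitivity analyses, with GP-only prescribing as a scenario.

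As a secondary scenario, pair each professional-led pathway with the same professional prescribing without the test, and report test and skill-mix effects separately. Do not rank pathways on this pairing, because each would then have a different baseline.

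The cost is one extra input and one scenario in an Excel model that is still described as to be developed. Non-GP-led pathways may look less favourable against standard care than under the GP-only baseline.
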